### Year 2: feasibility testing

Lay counsellors will be from the local areas, have at least a master’s qualification in psychology or a related discipline and experience in working with young people and/or schools. Prior to the launch of the feasibility study, they will receive full training over 3 months by a clinical psychologist on the team, supported by another team member experienced in training lay counsellors. Trainees will deliver multiple mock sessions of intervention delivery to support readiness for delivery in schools and quality control. The feasibility study will run in eight schools, with three randomly assigned to waitlist. The four interventions will run in parallel in schools. Lay counsellors will complete weekly monitoring logs of intervention delivery in each school, including logging of modifications made (as per FRAME^48^) and will have weekly supervision by clinical team members. Fidelity monitoring will be undertaken by a team of trained data collection assistants who have been heavily involved in the intervention development stage and will be highly familiar with the implementation protocol. Fidelity monitoring reports will be discussed frequently with the research manager to identify needs for lay counsellor action/support or intervention modification (see WP5).

We have established preliminary feasibility indicators for each intervention, which will be updated when interventions are finalised. Feasibility indicators which will be common across WP1–4 interventions are: meeting recruitment and retention rates, delivery as intended, measure completion and no significant adverse effects. We will adopt a ‘traffic light’ system for recruitment and retention as follows: red—if rates below 50% (say) then will not proceed; amber—if rates 50%–65% then proceed if there are plans to improve; green—above 65% proceed to definitive trial. Mixed-methods process and evaluation data will be secured for all interventions from adolescents, teachers, parents and lay counsellors to explore: perceived usefulness of the interventions; implementation challenges; unintended negative effects; safeguarding challenges; the process of change and intervention development needs. Evaluation outcomes will inform intervention improvements and parameters for a definitive trial.

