### Sample size calculation

The planned sample for the feasibility study by intervention is detailed in table 2. The minimum recommended sample size for a feasibility study is 30.^49^ The smallest group of participants are teachers (for the WP2 intervention). To secure a sample of 30, we will need to recruit a minimum of 8 schools, from which we will then be able to recruit approximately n=960 grade 9 adolescents (for WP1 intervention). Given this adolescent sample size, we have been able to calculate power in relation to WP1, where a key aim is to test two candidate primary outcomes measures—the Strengths and Difficulties Questionnaire (SDQ)^50^ and the Revised Child Anxiety and Depression Scale (RCADS).^51^ SDQ is an emotional and behavioural screening tool, culturally validated in India and used widely in adolescent mental health research. RCADS measures anxiety and depression and demonstrates excellent sensitivity to change. A translated RCADS has been used with Indian populations^52^ but full cultural validity needs to be established. As this will be an important tool to strengthen Indian mental health research, we will conduct a full validation study in parallel to the codesign stage. We have determined via a UK school feasibility trial^53^ that the change in SDQ had a SD of 2.8 points. Assuming 80% recruitment, comparing the mean changes in SDQ from 480 participants from the intervention group with 288 from the waitlist group using a 1% significance level has more than 98% power to detect a difference of 1 point on the SDQ Scale. Around 960 adolescents will be approached for WP1. At 65% recruitment, the power remains over 95%. This calculation is based on an analysis of variance approach, that is, regressing the change in SDQ on the intervention status (intervention or waiting list). The power achieved from an analysis of covariance approach, which regresses the final SDQ Score on baseline and intervention status, should be similar. Should the mechanism of the WP1 intervention be similar across population subgroups, we can therefore show good power. There may, however, be differences in the operation of the intervention between subgroups, such as government versus private schools. In that case, assuming an even division of samples, the power becomes 85% with 80% recruitment and 78% with 65% recruitment. A significance level of 1% is used rather than 5% since the sensitivity of the outcome measures is sought to be compared—that is, the SDQ will be compared in sensitivity in this setting with the RCADS.

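### The WP1 power figures allow for recruitment but not for loss to follow-up, so they hold only if nearly every recruited pupil gives a 3-month SDQ score.

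*Protocol article*

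**What the plan says.** The protocol article, under Sample size calculation, sets out power for WP1 as follows.

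- It takes a UK school feasibility trial as its source for variability: "the change in SDQ had a SD of 2.8 points".
- For 480 intervention and 288 waitlist pupils, at an assumed 80% recruitment, it claims that a comparison of mean changes "using a 1% significance level has more than 98% power to detect a difference of 1 point on the SDQ Scale".
- It then adds "At 65% recruitment, the power remains over 95"%.
- For subgroups of half the size, such as government and private schools, it gives 85% at 80% recruitment and 78% at 65%.
- The 1% level is explained by the wish to compare the SDQ with the RCADS. Whether the test is one- or two-sided is not stated.

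The same paragraph describes 960 in two ways: "we will then be able to recruit approximately n=960 grade 9 adolescents" and, later, "Around 960 adolescents will be approached for WP1".

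The section Year 2: feasibility testing applies one traffic light to recruitment and to retention, ending with "green—above 65% proceed to definitive trial". The data analysis plan for WP1–5 makes the primary analysis an ANCOVA of the 3-month outcome on baseline.

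**The concern.** A change score needs two measurements, and the ANCOVA needs a 3-month outcome. A pupil who is recruited but not measured at 3 months adds nothing to the comparison for which power is quoted. The power figures nevertheless step from pupils approached to pupils compared with a recruitment rate alone.

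The plan itself treats retention as uncertain enough to be a progression indicator, and tests power at 65% for recruitment but not for retention. The reassurance therefore covers only one of the two losses that the plan expects to monitor. The section goes on to conclude that power is good, and the study is meant to supply parameters for a definitive trial. A calculation without attrition is a poor model for that trial, and readers will take the quoted power as what this design delivers.

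**Working it through.** **Inputs.** Difference 1 SDQ point, SD of change 2.8, significance level 1% (Sample size calculation). Eight schools, three on waitlist (Year 2: feasibility testing), with 120 pupils per school (Table 2). Pupils approached are therefore 5 x 120 = 600 intervention and 3 x 120 = 360 waitlist, 960 in all.

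**Formula.** SE = 2.8 x sqrt(1/n1 + 1/n2). Power = Φ(1/SE − z), with z = 2.576 two-sided or 2.326 one-sided (normal approximation; the opposite tail is negligible). Like the plan's own figures, this is at individual level and makes no allowance for clustering.

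**Step 1: reproduce the stated figures.**

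- 80% recruitment: 0.80 x 600 = 480 and 0.80 x 360 = 288. SE = 0.2087, 1/SE = 4.792, power 98.7% two-sided. This matches more than 98%.
- 65% recruitment: 0.65 x 600 = 390 and 0.65 x 360 = 234. SE = 0.2315, 1/SE = 4.319, power 95.9% two-sided. This matches over 95%.

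Recruitment accounts for the whole reduction from 960, so both results assume 100% retention. A noncentral t calculation gives 98.6% and 95.8%, so the approximation is not an issue.

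**Step 2: apply retention.** Multiply both arms by the retention rate.

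| Recruitment | Retention | Analysed | Power, two-sided | Power, one-sided |
|---|---|---|---|---|
| 80% | 100% | 480 v 288 | 98.7% | 99.3% |
| 80% | 80% | 384 v 230 | 95.6% | 97.5% |
| 80% | 65% | 312 v 187 | 90.1% | 93.8% |
| 65% | 100% | 390 v 234 | 95.9% | 97.7% |
| 65% | 95% | 370 v 222 | 94.9% | 97.0% |
| 65% | 90% | 351 v 211 | 93.6% | 96.2% |
| 65% | 80% | 312 v 187 | 90.1% | 93.8% |
| 65% | 65% | 254 v 152 | 81.8% | 87.6% |

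In the last row, 960 x 0.65 x 0.65 = 406 pupils are analysed, about 42% of those approached.

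**Step 3: retention needed.** Two-sided power of 95% needs about 596 analysed pupils. That is 596/624 = 95.5% retention at 65% recruitment, or 596/768 = 77.6% at 80% recruitment. One-sided, at 65% recruitment, the requirement is just under 85%.

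**Step 4: halved subgroups.**

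| Recruitment | Stated | Full retention, one-sided | Full retention, two-sided | 65% retention, one-sided | 65% retention, two-sided |
|---|---|---|---|---|---|
| 80% | 85% | 85.6% | 79.2% | 66% | 56% |
| 65% | 78% | 76.7% | 68.4% | 55% | 46% |

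The stated subgroup figures sit near the one-sided column at full retention, whereas the whole-sample figures are close to the two-sided values. Measured from the one-sided basis, 65% retention costs about 20 points (85.6% to 66%) and about 22 points (76.7% to 55%).

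**The case against.** Several points on the other side are sound.

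- **The arithmetic is not wrong.** Both whole-sample figures follow from their inputs, and the quoted sentence is conditional on recruitment. The fault is an unstated assumption of complete follow-up. A fuller protocol or SAP might discuss attrition. That would not change what the published figures count, which is every recruited pupil.
- **Green is a range.** A reader might infer that the stated power fails in any study that meets the green criteria. It does not: 80% recruitment with 80% retention is green on both and still gives 95.6%. The 82% figure belongs to the lowest corner, and exactly 65% is amber under the plan's rule.
- **The traffic light is a progression rule.** A reader might take 65% as the retention that the team expects. Nothing in the document says so; the indicators are described as preliminary. Here 65% serves only as a stress test at the plan's own boundary.
- **Retention does not explain the whole subgroup gap.** Setting 56% and 46% directly against the stated 85% and 78% would be misleading, because the two-sided values at full retention are already 79% and 68%. That part of the gap is a matter of sidedness.
- **Table 2 need not change.** All Grade 9 pupils receive WP1 and may opt out of data collection, so 960 is a reasonable number for a universal programme. Only the two descriptions within the sample size paragraph conflict, and the recruitment rates make the intended meaning plain.
- **The consequence is limited.** The number of schools was set by the teacher target, not by power, and about 82% at a 1% level is still a conventional power.

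These points limit the weight of the concern. They do not supply the missing retention allowance.

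**Conclusion.** The point holds as an optimistic statement of power, to be corrected in the text. The whole-sample figures are right for complete follow-up and too high otherwise. Two-sided at 65% recruitment, the claim of over 95% already fails at 95% retention (94.9%) and falls to about 82% near the green boundary. At 80% recruitment, more than 98% becomes 95.6% at 80% retention and about 90% near 65%. Sidedness does not rescue the claim at the boundary: one-sided power at 65% recruitment and 65% retention is 87.6%. The subgroup figures are the most fragile, at about 66% and 55% one-sided near 65% retention.

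This rests on the plan's own SD, difference, significance level and 5:3 allocation, on equal retention in both arms, and on individual-level variance. The document states no expected retention, so the results are a range and not a forecast.

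**What to change.** In the sample size section:

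1. State a retention assumption and give power for pupils with both baseline and 3-month scores, as approached x recruitment x retention. Show at least 80% x 80%, 80% x 65% and 65% x 65%; on the present inputs these give 95.6%, 90.1% and 81.8% two-sided.
2. State whether the 1% test is one- or two-sided, and put the whole-sample and subgroup figures on the same basis.
3. Describe 960 as pupils approached throughout that paragraph. Table 2 can stay as it is.

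The cost is rewording and less favourable figures. Recruitment, delivery and data collection do not change.

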### School recruitment

We will recruit eight schools in Kolar and Bangalore to participate in both the codesign and feasibility stages of SAMA (WP1–6). School recruitment will be facilitated by the Karnataka State Primary and Secondary Education Ministry and the Karnataka State Secondary School Headmaster’s Association. We will recruit two school types (government and low-cost private) to identify school factors that may affect feasibility. Schools will be eligible to take part in SAMA if they endorse the delivery of WP1–6 in their schools, including participation in codesign. WP1 intervention feasibility testing will be with a new grade 9 cohort not involved in codesign.

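### The subgroup powers of 85% and 78% cannot both come from the plan's own inputs: a two-sided 1% test gives about 79% and 68%, a one-sided 1% test about 85% and 76%

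*Protocol article*

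**What the plan says.** All the power inputs stand in the Sample size calculation section of the protocol article. The outcome is the change in SDQ, and a UK school feasibility trial is cited for the spread: "the change in SDQ had a SD of 2.8 points". The main calculation is at 80% recruitment, "comparing the mean changes in SDQ from 480 participants from the intervention group with 288 from the waitlist group", and "using a 1% significance level has more than 98% power to detect a difference of 1 point on the SDQ Scale". At 65% recruitment the section puts power above 95%. It describes the calculation as an analysis of variance, with the change score regressed on arm. It does not say whether the 1% level is one-sided or two-sided.

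The section then allows that the intervention may operate differently across subgroups, with government versus private schools as the example. For that case it gives new figures: "assuming an even division of samples, the power becomes 85% with 80% recruitment and 78% with 65% recruitment".

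On the school types, the School recruitment section says: "We will recruit two school types (government and low-cost private) to identify school factors that may affect feasibility". The section Year 2: feasibility testing randomises three of the eight schools to waitlist. The number of schools of each type is not given.

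**The concern.** The subgroup figures should follow from the full-sample figures by halving both arms and keeping everything else fixed. Halving the sample divides the noncentrality parameter by the square root of 2. Starting from a two-sided power just under 99%, that brings power below 80%, not to 85%. The drop between the two recruitment levels also looks too small: the stated pair falls by 7 points, while the inputs imply a fall of 9 to 11.

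At stake is how a reader judges the subgroup fallback. As printed, one figure is above the customary 80% and the other just below it. On the usual two-sided reading both are below 80%, and the one at 65% recruitment is well below. That recruitment level is the boundary between amber and green in the plan's own traffic-light system, so it is a realistic case. A later trial that carries these figures forward would overstate what half the sample can show.

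**Working it through.** **Inputs, all from the Sample size calculation section**
- Difference 1 SDQ point; SD of change 2.8; significance level 1%.
- 80% recruitment: 480 vs 288 (stated).
- 65% recruitment: 960 × 0.65 = 624. The 5:3 split of schools gives 624 × 5/8 = 390 and 624 × 3/8 = 234.
- Subgroup under an even division: half of each arm, so 240 vs 144 and 195 vs 117.

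**Formula.** SE = 2.8 × √(1/n₁ + 1/n₂) and ncp = 1/SE. By the normal approximation, power = Φ(ncp − z), with z = 2.576 for two-sided 1% and z = 2.326 for one-sided 1%. The noncentral t is a check. For two groups, the non-directional analysis of variance F test is equivalent to the two-sided t test.

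**Step 1: the plan's full-sample figures**

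| n₁ vs n₂ | SE | ncp | Two-sided 1%: normal / t | One-sided 1%: normal / t | Plan |
|---|---|---|---|---|---|
| 480 vs 288 | 0.2087 | 4.792 | 98.7% / 98.6% | 99.3% / 99.3% | more than 98% |
| 390 vs 234 | 0.2315 | 4.319 | 95.9% / 95.8% | 97.7% / 97.6% | over 95% |

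Both readings satisfy the stated lower bounds. The two-sided values lie closer to them.

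**Step 2: the subgroup figures**

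| n₁ vs n₂ | SE | ncp | Two-sided 1%: normal / t | One-sided 1%: normal / t | Plan |
|---|---|---|---|---|---|
| 240 vs 144 | 0.2951 | 3.388 | 79.2% / 78.7% | 85.6% / 85.3% | 85% |
| 195 vs 117 | 0.3274 | 3.054 | 68.4% / 67.8% | 76.7% / 76.3% | 78% |

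Two-sided, the stated figures are too high by about 6 points (85 − 79) and 10 points (78 − 68). One-sided, 85% is matched and 78% is about 1.5 points too high.

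**Step 3: is there any one significance level that gives both?** Solve two-sided α = 2 × [1 − Φ(ncp − z_power)], normal approximation.
- 85% with 240 vs 144: 3.388 − 1.036 = 2.352, so α ≈ 0.019.
- 78% with 195 vs 117: 3.054 − 0.772 = 2.282, so α ≈ 0.022 (0.023 by noncentral t).

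Rounding does not close the gap. The largest α compatible with a printed 85% comes from 85.5%: 3.388 − 1.058 = 2.330, α ≈ 0.0198. The smallest compatible with a printed 78% comes from 77.5%: 3.054 − 0.755 = 2.299, α ≈ 0.0215. The two ranges do not meet.

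**Step 4: another reading of an even division.** If each half were also split equally between arms (768/4 = 192 per arm, or 624/4 = 156 per arm), power would be 82.2% and 71.9% two-sided, or 88.0% and 79.6% one-sided (normal approximation). Neither pair is 85% and 78%.

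**Step 5: whole schools.** Three waitlist schools shared between two types cannot give 1.5 each, so one type has at most one waitlist school. The halves of 240 vs 144 are therefore nominal for the school-type example.

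**The case against.** The strongest reply is that the article never says the test is two-sided. A one-sided 1% test reproduces the 85%, comes within 2 points of the 78%, and satisfies both full-sample statements, which are only lower bounds. This stands, and it limits the point. A reader might infer that the full-sample figures rule out a one-sided test. They do not: 99.3% and about 97.6% are also more than 98% and over 95%. Two-sided is the natural reading of an analysis of variance and the closer fit, but it is not proven. The reply does not rescue the 78%, which neither reading gives.

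A second reply is that the even division is openly an assumption and school type only an example. That is fair. The point about three waitlist schools calls for a caveat in the text and shows no arithmetic error.

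A third is that these powers decide nothing. The eight schools follow from the need for about 30 teachers, power was computed afterwards for the resulting adolescent sample, and progression rests on feasibility indicators, with traffic-light thresholds for recruitment and retention. This also stands, and it sets the weight of the point.

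**Conclusion.** The point holds as a moderate correction of a stated figure. On the plan's own inputs the subgroup powers are about 79% and 68% with a two-sided 1% test, or about 85% and 76% with a one-sided one. No single level gives the printed pair, so at least one of the two figures is wrong on any sidedness. The result assumes that the even division means half of each arm and that SD, difference and level are unchanged. It treats adolescents as independent, as the plan's calculation does, so correlation within schools is not reflected in any of these figures.

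Three stronger readings are not supported. A reader might infer that the plan claims power to detect a difference in effect between school types. It does not: its figures read as power within half the sample, and no interaction test is proposed. A reader might also infer that one school type could be left with no waitlist school. That needs an assumed number of schools per type and an unrestricted draw, and a restriction on the randomisation may well stand in a fuller protocol. Finally, nothing here shows the sample size or the progression rule to be wrong.

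**What to change.** In the Sample size calculation section:
1. State that the 1% level is two-sided and replace 85% and 78% with 79% and 68%. If a one-sided test was intended, say so and give 85% and 76%. The full-sample statements can stay under either choice.
2. Label the two figures as individual-level power within one subgroup of half the sample, with clustering by school ignored.
3. Add that three waitlist schools cannot be split equally between two school types, so the even division is only nominal for that example and results by school type will be read as descriptive.

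The cost is one or two numbers and about two sentences. No participants, schools or analyses are added, and the progression criteria stay as they are.

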#### WP5: implementation research

We will test the feasibility of our codesigned implementation approach, which will draw on improvement science. Lay counsellors will be trained and supported to optimise the intervention in situ by logging and overcoming implementation challenges as they arise, while keeping fidelity to intervention function. Process evaluations based on interviews/focus groups and implementation assessment tools will be conducted post intervention with key school staff and other stakeholder as needed depending on what challenges arise. Solutions to implementation challenges will be sought.

#### WP6: health economic evaluation

Using a micro (bottom-up) costing strategy,^54^ separate design and delivery costs per intervention component will be estimated using available data sources (eg, government ministry data, national pay scales, national earnings surveys) to determine unit costs for personnel time. Any additional primary data needs will be identified. Costs will be presented at the class and school level to promote generalisability. Preference-based outcome health and well-being measures are needed for economic evaluation^55^ but there is limited evidence on their use with adolescents and no evidence of their use feasibility in this context (with adolescents in school-based settings and in India). We will feasibility test candidate measures including Child Health Utility (CHU)-9D^56^ and EQ-5D-Y^57^ via pre–post administration to 50 intervention adolescents and via 10 think-aloud interviews to identify completion challenges (a satisfactory sample size given the richness of interview data). We will also administer the EQ-5D-5L^58^ and the ICEpop CAPability measure for Adults (ICECAP-A)^59^ pre and post intervention to 50 parents to determine measure completion and any need for instrument adaptation. These sample sizes are not selected to estimate the significance of a specific outcome, but to balance the desire to not overburden individuals while still informing completion rates of instruments and items. We will use the cost and outcome data to generate exploratory cost–consequence analyses of the intervention strategies.

#### WP7: understanding barriers and opportunities for research to policy uptake

We aim to (1) understand facilitators, barriers and solutions to policy uptake of the evidence on school mental health (in Karnataka); (2) identify ways of increasing adolescents’ participation in policy processes and (3) identify the potential for application of solutions to other states. A policy and stakeholder mapping exercise will be undertaken, and then key advisors (n~10) for each of the three policies (two national and one state)^29^ will be purposefully identified and interviewed. Insights will be shared at a stakeholder event comprising about 20 education and health decision-makers, adolescents and teachers to generate solutions for policy improvement. Insights will direct a social media campaign for policy action. Evaluation of effectiveness will be based on the number and nature of stakeholders reached, new knowledge on evidence-to-policy barriers and solutions and adolescents’ participation.

